# (Cost-)effectiveness of a combined lifestyle intervention integrated into standard care for low back pain compared to usual care for people with persistent non-specific low back pain who are overweight or obese: Protocol for a randomised controlled trial with parallel economic and process evaluations (Back2Health)

**DOI:** 10.1016/j.conctc.2026.101676

**Published:** 2026-08-01

**Keywords:** Physiotherapy, Rehabilitation, Low back pain, Lifestyle, Randomised clinical trial

## Abstract

**Background:**

Low back pain is often influenced by unhealthy lifestyle factors, such as physical inactivity, poor sleep, unhealthy diet, and excess weight. Despite their impact, these factors are rarely addressed in routine care for non-specific low back pain. In the Netherlands, adults with overweight or obesity can access a combined lifestyle intervention targeting physical activity, diet, sleep and stress. Integrating this intervention into standard care for non-specific low back pain may improve patient outcomes.

**Methods:**

The Back2Health study is a two-armed randomised controlled trial with parallel economic and process evaluations evaluating the (cost-)effectiveness of an integrated lifestyle intervention versus usual care on physical functioning and physical activity over 36 months in patients with persistent non-specific low back pain and overweight or obesity. In total, 318 adults will be recruited from Dutch hospitals and randomised (1:1) to either the integrated lifestyle intervention, delivered by physiotherapists trained as lifestyle coaches, or usual care.

Co-primary outcomes are physical functioning and physical activity (steps/day) over 36 months. Secondary outcomes include pain intensity, systemic inflammation markers, sleep, and diet. Participants complete questionnaires every 3-6 months and attend in-person physical assessments at five timepoints. Data will be analysed according to both ‘intention-to-treat’ and 'per-protocol' principles. Additionally, a process and economic evaluation will be performed.

**Ethics and dissemination:**

The study protocol was approved by a medical ethics committee (METC Brabant: NL85373.028.23). Results will be published in peer-reviewed journals and presented at (inter)national conferences.

**Trial registration number:**

ClinicalTrials.gov (NCT06594796).

## Background

1

Low back pain (LBP) represents a global healthcare challenge, being the predominant cause of years lived with disability worldwide. In 2021 alone, LBP was responsible for 70.2 million disability-adjusted life years worldwide [1]. The burden of LBP is exacerbated by various unhealthy lifestyle factors, including physical inactivity, stress, poor sleep, excess weight, and an unhealthy diet [[2], [3], [4], [5], [6], [7], [8], [9]].

International clinical guidelines recommend a conservative, non-pharmacological approach as first-line management for low back pain, emphasizing patient education, remaining active, and exercise within a biopsychosocial model of care [10]. Although lifestyle-related factors such as physical inactivity, obesity, smoking, sleep disturbances, and stress may contribute to the development and persistence of LBP, they are only briefly addressed due to limited evidence and implementation strategies. Similarly, in the Netherlands, LBP management focuses on primary care physiotherapy, exercise therapy, and general practitioner care according to guidelines to from the Royal Dutch Society of Physiotherapy (in Dutch: Koninklijk Nederlands Genootschap voor Fysiotherapie (KNGF)) [11] and the Dutch College of General Practitioners (in Dutch: Nederlands Huisartsen Genootschap (NHG)) [12]. While these guidelines encompass education, pain management, exercise therapy, and behavioural treatment, they do not address lifestyle-related issues in detail, due to limited evidence for these domains.

When primary care fails to relieve symptoms or an underlying pathology is suspected to cause LBP, patients are often referred to hospitals or rehabilitation centres for further evaluation and treatment. Approximately 65% of patients visiting hospitals in the Netherlands for LBP are overweight or obese [13]. These patients face increased disability, lower belief in the importance of physical activity, and heightened absenteeism, resulting in substantial societal costs [14,15]. This group of patients is often referred back to primary care, because medical specialists typically have limited treatment options to offer [16,17].

Recognizing the imperative to address both lifestyle and clinical factors becomes apparent in managing this subset of LBP patients. Such a combined approach may not only improve clinical outcomes, such as reducing pain and enhancing function, but can also offer broader health benefits by lowering the risk of diabetes and cardiovascular diseases [18,19]. This perspective aligns with recommendations from The Lancet series on LBP, which emphasize integrated, patient-tailored management strategies rather than isolated treatments [10].

Since 2019, overweight or obese adults in the Netherlands can follow a combined lifestyle intervention that incorporates guidance on physical activity, dietary habits, sleep, and stress [[20], [21], [22]]. In addition to individual- and group sessions, the intervention also incorporates evidence-based behavioural change techniques, such as eHealth self-monitoring, activity tracking, goal setting, action planning, and relapse prevention to increase effectiveness [[20], [21], [22], [23], [24]]. While conventional treatments such as exercise, education, and medication (i.e., usual care) have demonstrated effectiveness in managing persistent LBP [10,25], their effect sizes remain modest [26,27]. International studies have shown the potential of lifestyle interventions delivered by physiotherapists to be (cost)-effective compared to usual care, particularly in overweight or obese patients with persistent LBP [9,28]. However, these studies primarily evaluated short-term interventions, targeted only a limited number of lifestyle factors, and did not integrate the lifestyle intervention into routine guideline-based LBP care, limiting their applicability to everyday clinical practice.

This pragmatic study, referred to as Back2Health, will investigate the effectiveness of a combined lifestyle intervention integrated into standard care for non-specific LBP according to Dutch guidelines for patients with persistent non-specific LBP who are overweight or obese compared to usual care on self-reported physical functioning and physical activity levels over 36 months. The study specifically targets patients who are overweight or obese, as these individuals are currently eligible for a combined lifestyle intervention that is fully reimbursed through the Dutch basic health insurance package, providing an opportunity to integrate lifestyle supportwithin standard LBP care. Self-reported physical functioning and physical activity were selected as the primary outcomes because they align with the main aims of the Back2Health intervention: improving daily functioning and promoting a more active lifestyle. Physical activity is also considered a key mechanism for achieving long-term benefits. Additionally, cost-effectiveness of the intervention compared to usual care will be evaluated. A process evaluation will be conducted alongside the trial to study the implementation of the intervention into clinical practice.

## Methods

2

### Study design

2.1

The Back2Health study is a pragmatic multi-centre, two-arm, prospective randomised controlled trial with a superiority design. The Standard Protocol Items: Recommendations for Interventional Trials (SPIRIT) statement has been used for reporting [29]. The pragmatic design was chosen to evaluate the effectiveness, cost-effectiveness and implementation of the intervention under routine clinical conditions in the Netherlands, where eligible individuals with overweight or obesity can access fully reimbursed combined lifestyle interventions and choose between several nationally approved programmes [11,12,[20], [21], [22]]. Accordingly, flexibility in intervention delivery and co-interventions is preserved to reflect usual care and enhance the generalisability of the findings. The latter is particularly important when cost-effectiveness is also evaluated, because economic evaluations aim to inform real-world decision-making and therefore require estimates of costs and effects that are representative of routine clinical practice.

### Participants

2.2

Patients will be recruited from secondary hospitals throughout the Netherlands from January 2025 till December 2026.

Overweight or obese patients with persistent (≥3 months) non-specific LBP, who experience decreased physical functioning, and are referred back from hospital care to primary care, are eligible for inclusion. Patients need to be at least 18 years of age and have either a body mass index (BMI) ≥30 (i.e., obese) or a BMI ≥25 (i.e., overweight) with at least one of the following factors: osteoarthritis, sleep apnea, risk factors for cardiovascular diseases or type 2 diabetes in line with the reimbursement criteria for combined lifestyle interventions in the Netherlands [30]. Non-specific low back pain was defined according to the Dutch general practice and physiotherapy guidelines as low back pain without a clearly identifiable specific anatomical or pathological cause explaining the symptoms [11,12]. Classification into specific or non-specific low back pain was made by the recruiting medical specialist based on clinical assessment, history, physical examination, and available diagnostic information in accordance with routine clinical practice. Additionally, patients need to experience an average LBP intensity of ≥3 out of 10 on a numeric pain rating scale (NPRS) over the past week and a physical functioning score of ≥4 out of 24 on the Roland-Morris Disability Questionnaire (RMDQ).

Patients will be excluded if they are diagnosed with specific LBP (e.g., fracture, radiculopathy, tumour, or infection), have a psychiatric condition that, in the clinical judgment of the recruiting medical specialist, is considered likely to interfere with study participation (e.g., schizophrenia), are currently pregnant, or are less than nine months postpartum. No predefined diagnostic criteria or questionnaire cut-off scores were used for this exclusion criterion.

### Intervention

2.3

#### Experimental group: Combined lifestyle intervention

2.3.1

The experimental group will follow one of five nationally-registered combined lifestyle interventions (i.e., BeweegKuur, Coaching op Leefstijl (CooL), SLIMMER, Samen Sportief in Beweging (SSIB) or X-Fittt), integrated into standard care for LBP, according to Dutch clinical guidelines for LBP [11,12,[20], [21], [22]]. The overall aim of the combined lifestyle intervention is to counsel participants who are obese or overweight to help them achieve a healthier lifestyle. For the purpose of this study, the intervention was delivered by physiotherapists who are additionally certified as lifestyle coaches through a accredited training programme. This training includes formal education, supervised practice, and competency assessment in behaviour change techniques. The intervention is based on the Dutch combined lifestyle intervention (GLI), in which motivational interviewing is the primary behaviour change technique, supplemented by goal setting, action planning, and problem solving. These techniques are applied as part of routine clinical practice by certified lifestyle coaches. The programs follow a personalised approach, guiding participants to explore their current lifestyle habits and how these affect their well-being, and set goals to adopt healthier behaviours. They are stimulated to take responsibility and remain in charge of their personal goals. The intervention spans two years. During the first six to twelve months, sessions focus on identifying unhealthy behaviours related to physical activity, diet, sleep, and stress, and on supporting participants in making sustainable lifestyle changes. The remaining months of the program emphasize goal monitoring and the maintenance of newly adopted lifestyle habits. The program consists of both individual and group sessions; however, the exact contact moments, frequency, and specific content or structure of the sessions will differ between the various combined lifestyle interventions.

In addition to the combined lifestyle interventions, the participants will receive standard care for LBP according to the national guidelines of the Royal Dutch Society of Physiotherapy [11] and the Dutch College of General Practitioners [12]. These guidelines recommend an active approach to treatment, including paineducation (i.e., education about low back pain, prognosis, and self-management) and exercise therapy [11,12]. It might also include behavioural interventions or non-exercise therapy interventions, depending on the individual treatment goals and dominant prognostic factors. Participants also maintain access to other usual care options during the study period, such as pain medication and hospital treatment.

#### Control group: Usual care

2.3.2

The control group will receive care as recommended by the medical specialist, which may range from a watchful waiting approach to referral for physiotherapy, exercise therapy or general practitioner care, in accordance with current Dutch guidelines for LBP according to the Royal Dutch Society of Physiotherapy [11] and the Dutch College of General Practitioners [12]. It may also involve re-entry to the hospital after failed treatment in primary care. Similar to the intervention group, usual care follows a guideline-based, predominantly active approach that may include education and exercise therapy. However, it is delivered in routine clinical practice without the structured, multidisciplinary lifestyle coaching programme, predefined two-year follow-up structure, or systematic use of behaviour change techniques that are central to the intervention group.

### Randomisation, blinding and treatment allocation

2.4

Participants will be randomised with a 1:1 ratio using a central computer-generated randomisation program by an independent researcher not involved in the study. A block randomisation approach (alternating block sizes of 6 and 4) will be used. Randomisation will be conducted after providing informed consent and completing the baseline measurement. Participants will be informed orally about their allocation. Treating medical specialists and general practitioners will be informed about the allocation of the participant. In this type of study, blinding patients and healthcare providers is not feasible; however, data analysis will be conducted by an investigator who is blinded to group assignments.

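### Block sizes alternate in a fixed 6-4 order in an open-label trial, so an observer of the whole sequence could be certain of up to about 28% of allocations; a specialist at one hospital probably far fewer

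*Protocol article*

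**What the plan says.** Section 2.4 (Randomisation, blinding and treatment allocation) describes the scheme in one sentence: "A block randomisation approach (alternating block sizes of 6 and 4) will be used". It does not say which size comes first, or whether there is one central list or one per hospital. No stratification by hospital is mentioned.

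The list is held away from the recruiters: "Participants will be randomised with a 1:1 ratio using a central computer-generated randomisation program by an independent researcher not involved in the study". The timing is also fixed: "Randomisation will be conducted after providing informed consent and completing the baseline measurement".

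Allocation is open once made. The section says that "blinding patients and healthcare providers is not feasible", and adds: "Treating medical specialists and general practitioners will be informed about the allocation of the participant". Only the data analyst is described as blinded.

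Section 2.1 calls the study a "pragmatic multi-centre, two-arm, prospective randomised controlled trial", without giving the number of hospitals. Section 2.2 leaves part of eligibility to clinical judgement: "Classification into specific or non-specific low back pain was made by the recruiting medical specialist based on clinical assessment". The psychiatric exclusion also rests on that specialist's judgement, without predefined criteria. On timing, section 2.2 says: "Patients will be recruited from secondary hospitals throughout the Netherlands from January 2025 till December 2026". The article that discloses the block sizes is dated 1 August 2026, inside that window.

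**The concern.** Block size is varied so that people who see past allocations cannot tell where a block ends. If 6 is always followed by 4 and 4 by 6, the boundaries are known to anyone who knows the rule and can count. Once one arm in a block is used up, every remaining assignment in that block is certain.

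In a blinded trial this would matter little. Here allocations are open, and two eligibility judgements belong to the recruiting specialist. There is also a conceivable reason to prefer one arm for a given patient. The Background says that the lifestyle programme is fully reimbursed for eligible patients, and the Discussion says that controls are asked not to join one. A recruiter who expects the next allocation to be control could delay an invitation or judge a borderline patient ineligible. The arms could then differ in ways that adjustment for measured baseline variables does not reliably remove. One co-primary outcome, the RMDQ, is self-reported by unblinded patients, so comparable arms matter all the more.

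**Working it through.** The article gives no predictability figure, so there is none to reproduce.

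**Inputs.** Block sizes 6 and 4 in fixed alternation, and 1:1 allocation (section 2.4); 318 patients (section 2.6); recruitment from January 2025 to December 2026, taken as 24 months (section 2.2); article date 1 August 2026. Assumptions: all balanced orders within a block are equally likely, hospitals are of equal size, and accrual is uniform.

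**1. Certain assignments for an observer of the full sequence.** In a block of size 2m, the expected number of assignments made after one arm is exhausted is 2m/(m+1).
- Block of 4 (m = 2): 4/3 = 1.33, or 33.3% of the block.
- Block of 6 (m = 3): 6/4 = 1.50, or 25.0% of the block.
- One 6+4 cycle: (1.50 + 1.33)/10 = 2.83/10 = 28.3%.
- 318 patients, starting with a 6: 31 full cycles (310 patients), one block of 6, and the first two places of a block of 4, which are never certain. 31 × 2.833 + 1.50 = 89.3, and 89.3/318 = 28.1%.

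Enumeration of all balanced orders gives the same values.

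**2. An observer who sees only one hospital's allocations on a shared list.** Simulation with K equal hospitals, generously giving the observer the block boundaries:

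| Hospitals (assumed) | Share certain |
|---|---|
| 2 | 5.1% |
| 3 | 2.1% |
| 5 | 0.6% |
| 8 | 0.2% |
| 10 | 0.15% |

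With a separate list per hospital, the share within each hospital returns to about 28%.

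**3. Effect of random ordering.** The observer sees every past allocation and knows the possible sizes but not their order (simulation):

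| Scheme | Certain | Best guess correct |
|---|---|---|
| 6 and 4 alternating | 28.3% | 69.3% |
| 4 and 6 in random order | about 5.4% | about 69% |
| 4, 6 and 8 in random order | about 2.3% | about 68% |

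The alternating best-guess figure is exact: expected correct guesses are 4.10 in a block of 6 and 2.83 in a block of 4, so 6.93/10. Random order removes most of the certainty but hardly changes how often a good guesser is right.

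**4. Patients still to be randomised at the article date.** August to December 2026 is 5 of 24 months: 318 × 5/24 = 66. Under the present scheme, 28.3% of 66 is about 19 certain assignments, and only for an observer of the whole sequence.

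**The case against.** A reader might infer that, because specialists are told allocations, specialists can know about 28% of assignments. The document does not support that. What section 2.4 describes is being told the allocation of the participant under their care. Randomisation is central, the trial is multi-centre, and no per-hospital list is stated. On a shared list a single specialist's certainty is the small share in the second step above. The eligibility discretion belongs to the recruiting specialist, while the 28% belongs to someone with sight of the full sequence, and no section shows one person with both. That research staff follow the running sequence is plausible but not stated. This objection stands, and it makes 28% an upper bound.

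The safeguards also count. The list is run by someone outside the study, and randomisation comes after consent and baseline. Baseline includes a nine-day activity-monitor protocol (section 2.5.1). If that wear must be finished first, uniform accrual gives about 318/730 × 9 = 3.9 randomisations between the eligibility decision and allocation, against a mean block of 5. On a shared list, the block position at the eligibility decision then says little about the position at randomisation. On slow per-hospital lists the lag would protect less. These points reduce the risk, but they do not remove it for anyone who can predict the next allocation when deciding on invitation, timing or eligibility.

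A condensed article may leave the list structure and starting block to the full protocol, so their absence is no finding here. The alternating order itself is stated, and it is this statement that is at issue.

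**Conclusion.** The point holds in a limited form. A fixed 6-4 order is a weak choice in an open-label trial and gives up most of the benefit of using two block sizes. Its reach is up to about 28% certain assignments, either for an observer of the whole sequence or within hospitals if lists are per hospital. For one hospital's specialist on a shared list it is about 5% with two equal hospitals and under 1% with five or more. The result rests on reading the sentence literally, on assumed hospital numbers of equal size, and on uniform accrual for the count of remaining patients. If the sizes were in fact drawn at random, section 2.4 misdescribes the method and needs only a correction.

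Nothing in the document shows that selection has occurred, and it would be wrong to infer that the comparison is already compromised. This is an inexpensive improvement to concealment for the rest of recruitment.

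**What to change.** For patients not yet randomised, have the independent researcher regenerate the remaining list with block sizes in random order. Keep the sizes and order from anyone who recruits or measures until recruitment closes, and amend section 2.4 to say so. The amendment should also state whether the list is shared or per hospital and who sees the running allocations, because these decide which of the figures above applies.

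The cost is one new list and a minor amendment. If sizes stay at 4 and 6, the maximum within-block imbalance stays at 3. Adding a block of 8 raises it to 4, and in exchange certain assignments fall further, from about 5% to about 2% for a full-sequence observer. The gain is confined to the patients still to come, roughly 66 at the article date and fewer later, and best-guess success stays near 69%. If recruitment is almost complete, stating plainly how the order was generated and who saw the allocations is still worthwhile.

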### Data collection and outcome measures

2.5

Data will be collected at nine time points over the 36-month study period (i.e., 2 year intervention and 12 months follow-up), during which participants are asked to complete all questionnaires digitally via CastorEDC every 3 to 6 months (i.e. baseline and 3, 6, 9, 12, 18, 24, 30 and 36 months) (Castor Electronic Data Capture. https://castoredc.com). Physical measurements will be performed at five time-points (i.e. at baseline and 6, 12, 24, and 36 months) during visits either at the hospital or physiotherapist office, depending on planning and participant preferences. A description of the outcomes and time frame of data collection is provided in Table 1.

